#### Exploratory outcomes

*Time from randomization to occurrence of myopia (time-to-event outcome)*: The time from randomization to the occurrence of myopia will be measured as a time-to-event outcome. This endpoint will provide further insights into how quickly DIST delays the onset of myopia compared to the control group.*The association between near-work duration at home and myopia onset*: The duration of near-work activities (e.g., reading, using electronic devices) at home will be correlated with the onset of myopia to investigate environmental factors influencing myopia development. This data will help clarify the role of lifestyle factors in conjunction with DIST intervention.*The association between device usage duration and myopia onset*: The duration of DIST device usage will be correlated with the onset of myopia to explore potential dose–response relationships. This will determine whether longer usage of DIST is associated with a greater effect on myopia prevention, while controlling for other near work behaviors.*Changes in choroidal thickness (ChT) (µm) at 6 and 12 months follow-ups*: Changes in choroidal thickness will be monitored as an exploratory endpoint to assess the potential underlying physiological mechanisms of DIST technology in myopia prevention. Changes in choroidal thickness or blood flow as biomarkers of myopia progression are of significant importance in myopia prevention and control research.*Side effects and adverse events*: The occurrence of side effects and adverse events will be closely monitored throughout the study to ensure the safety of the DIST intervention. This will include any ocular or systemic issues reported by participants, and the severity of these events will be recorded.

### Participant timeline {13}

Screening, baseline, and follow-up time points throughout the study followed a pre-determined schedule, as described in Table 1.

**Table 1 Tab1:** Timeline of screening, enrollment, and assessments

	Study period				
Procedure	Screening period	Enrolment	Post-assessments		
			3 months (± 14 days)	6 months (± 14 days)	12 months (± 14 days)
Informed consent	X				
Inclusion/Exclusion criteria	X				
General information and relevant medical history	X				
Questionnaire survey		X	X	X	X
Visual acuity(distant)	X		X	X	X
Sub-pupil computer refraction and cornea curvature	X		X	X	X
Sub-pupil subjective refraction	X		X	X	X
Slit-lamp examination	X		X	X	X
Fundus examination	X		X	X	X
Tonometry		X		X	X
Axial length		X	X	X	X
OCT		X		X	X
Paralyze the ciliary muscle		X		X	X
Computer refraction and cornea curvature^a^		X		X	X
Subjective refraction^a^		X		X	X

*OCT* optical coherence tomography

^a^With cycloplegia

### Sample size {14}

To ensure adequate power for detecting differences in myopia incidence between the two intervention groups and the control group, we performed a sample size calculation based on historical data and statistical assumptions. Below, we outline the key parameters and methodological considerations underlying our determination.

#### Outcome measure used for calculations

The primary outcome measure used for this calculation is the incidence of myopia, defined as the proportion of participants developing myopia over 1 year.

#### Test statistic

The test statistic employed is the Pearson chi-square statistic for comparing two independent proportions.

#### Null and alternative hypotheses

##### Null hypothesis (H_0_)

There is no difference in the incidence of myopia between the study arms.

##### Alternative hypothesis (H_1_)

The incidence of myopia in the experimental (intervention) groups is lower than that in the control group.

#### Type I error rate (alpha), power level (e.g., 80% power)

Type I error rate (α): 0.025/2 = 0.0125

Power (1-β): 80%

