### Trial design {8}

This study will be a randomized, superiority-controlled trial with a parallel-group design. One hundred ninety-two pre-myopic children will be randomly divided into three groups of 64 subjects in a 1:1:1 ratio. The three groups are no use of DIST, DIST alone (RIO-Max 2.0), and DIST optimized by combining the optical defocusing technique (RIO-Ultra 2.0). The complete study flowchart is shown in the figure (Fig. 1). The protocol and all study procedures are approved by the Medical Ethics Committee of the Affiliated Eye Hospital of Wenzhou Medical University (2024–016-K-015–05) and conducted following the ethical standards of the Declaration of Helsinki. The protocol has been registered with the Chinese Clinical Trial Registry (ChiCTR2400082078) and uses the SPIRIT reporting guidelines [25]. Subjects are required to sign an ethical informed consent form before participating in the experiment.

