#### Assumed event rate

Based on a previous retrospective study on the use of low-concentration atropine to prevent myopia onset in pre-myopic children [26], the assumed event rates for a dichotomous outcome are as follows:Control group: 54%Intervention group: 21%

These rates provide the basis for our assumption that a meaningful reduction in myopia incidence can be observed between groups.

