#### Sample size calculation

Using the Pearson chi-square statistic method, we calculated the necessary sample size per group. The software PASS 15.0 and G*Power 3.1 were used to verify the calculations.

Given:p₁ (control group event rate) = 0.54p₂ (intervention group event rate) = 0.21α = 0.0125, β = 0.20superiority margin = 0.05

The minimum required sample size per group is approximately 50 participants before adjusting for dropout rates.

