#### Adjustment for dropout and attrition

Considering an anticipated dropout rate of 20%, the final required sample size per group is the following:Adjusted sample size per group: 64 participants.Total sample size for three groups: 192 participants.

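### The only stated error rule for the two primary comparisons is a fixed split of alpha; a Holm step-down would keep the same nominal family-wise level and recover some power for one added sentence

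*Protocol article*

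**What the plan says.** Under Sample size {14}, the protocol article says that the trial is powered for "differences in myopia incidence between the two intervention groups and the control group", which makes two comparisons with a shared control. The alternative hypothesis is directional: "The incidence of myopia in the experimental (intervention) groups is lower than that in the control group". The error rate is then given as "Type I error rate (α): 0.025/2 = 0.0125", with 80% power. The same 0.0125 returns under Sample size calculation, together with rates of 54% and 21% and a superiority margin of 0.05, and leads to this result: "The minimum required sample size per group is approximately 50 participants". After allowance for 20% dropout, the trial has "three groups of 64 subjects in a 1:1:1 ratio".

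The section Statistical methods for primary and secondary outcomes {20a} names a covariate-adjusted logistic regression with trend analysis for the primary outcome. It gives neither a significance level nor a multiplicity rule for the two device-control comparisons. Bonferroni is named there only as one possible post hoc test for choroidal thickness, which is exploratory.

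**The concern.** The sample size section holds the document's only statement on type I error for the primary outcome. A reader looking for the decision rule will naturally take it to be 0.0125 for each device, whatever the other device shows.

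That rule protects the family-wise error, but it is not the most efficient way to do so. Holm's procedure tests the smaller of the two p-values at 0.0125 and, if that is significant, the larger at 0.025. It holds the same nominal family-wise level and rejects everything that the fixed split rejects, and sometimes more.

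Both comparisons matter here. The Objectives state the hypothesis in terms of DIST, and the abstract asks both for its independent effect and for the added benefit of the combination. Under Trial status, recruitment is reported as completed in September 2025, so power can no longer be gained by adding children. The planning rates come from a retrospective atropine study, not from this device. If one arm has a smaller effect than assumed, that arm's comparison has the most to gain from a step-down rule.

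**Working it through.** **Inputs from the protocol article.** Control rate 0.54, intervention rate 0.21, margin 0.05, alpha 0.025/2 = 0.0125, power 80%, dropout 20%, allocation 1:1:1.

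**Inferred.** The document does not say that 0.0125 is one-sided. The directional alternative points that way, and one-sided use reproduces the sample size.

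**Step 1: the plan's own figure.** For superiority by a margin with unpooled variance:

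n = (z₁₋α + z₁₋β)² × [p₁(1−p₁) + p₂(1−p₂)] / (p₁ − p₂ − margin)²

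- z₁₋α = 2.2414 and z₁₋β = 0.8416; their sum squared is 9.5054.
- Variance term: 0.54 × 0.46 + 0.21 × 0.79 = 0.2484 + 0.1659 = 0.4143.
- Denominator: (0.33 − 0.05)² = 0.28² = 0.0784.
- n = 9.5054 × 0.4143 / 0.0784 = 50.2, rounded up to 51, against a stated figure of about 50.
- Dropout: 51 / 0.8 = 63.75, rounded up to 64; 3 × 64 = 192.

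The stated sample size is reproduced. By the same formula, power per comparison is 79.8% at n = 50 and 80.7% at n = 51.

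**Step 2: the effect of Holm on the sample size.** The first step of Holm uses 0.025/2 = 0.0125, the level already used for sizing. The figures 51, 64 and 192 stay as they are.

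**Step 3: power under the two rules.** Three independent binomial arms of 51 share one control. The test is z = (p̂_control − p̂_device − 0.05) / SE with unpooled SE, and critical values 2.241 (for 0.0125) and 1.960 (for 0.025). The fixed split rejects a comparison if z > 2.241. Holm also rejects it if z > 1.960 and the other comparison has z > 2.241. Exact enumeration over all outcomes gives:

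| Control 54%; true device rates | Quantity | Fixed split | Holm |
|---|---|---|---|
| DIST 21%, Combined 21% | a given comparison | 79.0% | 84.0% |
| | both comparisons | 67.4% | 77.3% |
| | at least one | 90.6% | 90.6% |
| DIST 30% (assumed), Combined 21% | DIST | 40.6% | 49.1% |

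The 30% rate is not in the protocol; it illustrates a weaker effect of DIST alone.

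**Step 4: sensitivity to the margin.** The analysis section does not mention the margin. Without it (pooled z-test, n = 51), the planning rates give 89.9% against 93.4% per comparison and 83.0% against 90.1% for both. With DIST at 30% and Combined at 21%, DIST power is 57.7% against 70.4%. The direction is the same, and the levels are higher.

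**The case against.** The strongest reply is that the quoted line fixes a planning alpha and no more. It stands in the sample size section, and a trial that meant to use Holm would naturally be sized at exactly this level. A statistical analysis plan, not shown, may already contain a step-down rule. All of this stands. A reader might infer that the plan commits its primary analysis to plain Bonferroni; the document neither does so nor rules out Holm.

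A reader might also infer that the split is a mistake or that it costs the trial its planned power. Neither is supported. The split is a valid control of the family-wise error, and the sample size pays for 80% power per comparison at 0.0125. The power caveat in the Discussion refers to the lack of earlier studies with similar equipment, not to the division of alpha.

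Nor does the fixed split discard power for nothing. It gives simple simultaneous confidence intervals that agree with the tests, and a decision on each device that does not depend on the other.

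Finally, the levels are nominal. If only one arm works, the ineffective arm is declared effective in 2.9% of trials under Holm and 1.1% under the fixed split (pooled z-test, no margin, n = 51, control and ineffective arm at 54%, effective arm at 21%). The excess over 2.5% comes from the normal approximation at n = 51, not from the step-down, but the step to 0.025 is what exposes the trial to it.

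What survives is narrower: the only rule in print is one that a simple alternative improves on, and the analysis section does not say which rule will be used.

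**Conclusion.** The point holds as a suggestion for improvement. If the fixed 0.0125 is used as the decision rule, Holm would add about 5 percentage points of power per comparison and about 10 points for showing both effects at the planning rates, and about 8 points for DIST if its true rate were 30%. It would not raise the chance of at least one significant result.

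These figures assume one-sided testing, 51 evaluable children per arm, the 0.05 margin with unpooled variance, and the two-proportion test used for planning. The adjusted logistic regression may have somewhat different power.

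**What to change.** Leave the sample size section as it is. Add one rule to the primary outcome paragraph of the statistical methods: order the two one-sided p-values (DIST against control, Combined against control); test the smaller at 0.0125; only if it is significant, test the larger at 0.025. Report two-sided 97.5% confidence intervals for both comparisons, which leave 0.0125 in each tail. The rule should be fixed before the data are analysed.

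The cost is one sentence and no extra participants. There are two small drawbacks: the interval for the second comparison need not agree with its step-down test, and the decision on the second device depends on the result for the first. If the sponsor values matching intervals and separate decisions more than the added power, the fixed split remains acceptable, but the analysis section should then say that it is the decision rule.

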#### Assumed event rate

Based on a previous retrospective study on the use of low-concentration atropine to prevent myopia onset in pre-myopic children [26], the assumed event rates for a dichotomous outcome are as follows:Control group: 54%Intervention group: 21%

These rates provide the basis for our assumption that a meaningful reduction in myopia incidence can be observed between groups.

#### Sample size calculation

Using the Pearson chi-square statistic method, we calculated the necessary sample size per group. The software PASS 15.0 and G*Power 3.1 were used to verify the calculations.

Given:p₁ (control group event rate) = 0.54p₂ (intervention group event rate) = 0.21α = 0.0125, β = 0.20superiority margin = 0.05

The minimum required sample size per group is approximately 50 participants before adjusting for dropout rates.

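### The sample size uses a 5-point superiority margin that the hypotheses and the planned test do not contain, so the stated 80% power belongs to a different comparison; the error is conservative

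*Protocol article*

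**What the plan says.** The sample size section {14} of the protocol article sets these elements:

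- Null hypothesis: "There is no difference in the incidence of myopia between the study arms".
- Alternative: "The incidence of myopia in the experimental (intervention) groups is lower than that in the control group". It is directional and has no margin.
- Test: "The test statistic employed is the Pearson chi-square statistic for comparing two independent proportions".
- Error rate: "Type I error rate (α): 0.025/2 = 0.0125", with 80% power. Whether 0.0125 is one- or two-sided is not said.
- Assumed one-year incidence: 54% in control, 21% under intervention.
- Under Sample size calculation, the inputs are repeated and a superiority margin of 0.05 is added. The result follows: "The minimum required sample size per group is approximately 50 participants before adjusting for dropout rates". With 20% dropout this becomes 64 per arm, 192 in total.

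The margin appears nowhere else. Trial design {8} calls the trial a superiority trial without naming one. Statistical methods {20a} analyses the primary outcome by logistic regression with trend analysis, adjusted for baseline spherical equivalent, age and gender, again without a margin.

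**The concern.** A sample size describes a trial only if it was computed for the test that will be run. A test of no difference and a test of a reduction greater than 5 points have different nulls, different power at the same size, and in a band of results different verdicts. A reader of the protocol cannot tell which claim the 192 children were meant to support. If the margin was not intended, the stated power and the implied detectable difference do not belong to the planned comparison. If it was intended, nothing in the analysis enforces it: an ordinary chi-square does not test it, and an odds ratio compared with 1 cannot be set against a margin on the risk difference.

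**Working it through.** **Inputs (sample size section {14}).** p1 = 0.54, p2 = 0.21, difference 0.33; margin 0.05; alpha 0.0125; power 0.80; dropout 20%. Normal quantiles: 2.2414 (one-sided 0.0125), 2.4977 (two-sided 0.0125), 0.8416 (80% power). Unpooled variance sum: 0.54×0.46 + 0.21×0.79 = 0.2484 + 0.1659 = 0.4143. Pooled: mean rate 0.375, so 2×0.375×0.625 = 0.46875.

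**1. The stated figures, with the margin, one-sided, unpooled.**
n = (2.2414 + 0.8416)² × 0.4143 / (0.33 − 0.05)² = 9.505 × 0.4143 / 0.0784 = 50.2, so 51.
Dropout: 51/0.8 = 63.75, so 64. Both figures reproduce. (Exactly 50 would give 62.5, so 63.)

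**2. The same inputs without the margin.**
- One-sided, unpooled: 9.505 × 0.4143 / 0.33² = 36.2, so 37.
- One-sided, pooled: (2.2414×√0.46875 + 0.8416×√0.4143)² / 0.33² = 39.6, so 40; 46 with continuity correction.
- Two-sided: 43 unpooled, 47 pooled, 53 with continuity correction.

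None gives both 50 and 64. After dropout, two-sided 47 becomes 59 and 53 becomes 67. A two-sided 0.0125 with the margin, unpooled, needs 59 before dropout, so that reading does not reproduce the figure either. The margin therefore drives the stated number.

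**3. Power at 51 evaluable per arm, 54% versus 21%.** Standard error under the alternative: √(0.4143/51) = 0.0901. Pooled null standard error: √(0.46875/51) = 0.0959.
- Against the margin, one-sided: Φ(0.28/0.0901 − 2.2414) = Φ(0.865) = 80.7%.
- Against no difference, pooled, one-sided: Φ((0.33 − 2.2414×0.0959)/0.0901) = Φ(1.277) = 89.9%.
- Against no difference, pooled, two-sided: Φ((0.33 − 2.4977×0.0959)/0.0901) = Φ(1.005) = 84.2%.

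Exact enumeration of the pooled test at 51 per arm gives 89.9% and 84.3%.

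**4. Where the no-difference test reaches 80% power at 51 per arm.**
- One-sided: power is 81.8% at an intervention rate of 24% and 78.5% at 25%, so 80% falls at about 24.6%, a difference of about 29 points.
- Two-sided: 81.1% at 22% and 77.6% at 23%, so about 22.3%, a difference of about 32 points.

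**5. Results on which the two nulls disagree** (control observed at 54%, 51 per arm, one-sided 0.0125, which corresponds to a two-sided 97.5% interval).
- Difference 22 points (54% versus 32%): pooled z = 0.22/√(2×0.43×0.57/51) = 2.244, just above 2.241. Lower limit 0.22 − 2.2414×√((0.2484 + 0.2176)/51) = 0.006.
- Difference 25 points (54% versus 29%): pooled z = 0.25/√(2×0.415×0.585/51) = 2.562. Lower limit 0.25 − 2.2414×√((0.2484 + 0.2059)/51) = 0.038.

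Differences of about 22 to 25 points are thus significant against zero, while their lower limits, 0.6 to 3.8 points, do not clear 5 points.

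**The case against.** The strongest reply is that the discrepancy is harmless: under the protocol's own rates the planned comparison has more power than claimed, no child is added or lost, and recruitment is reported complete in September 2025. That stands, and it limits the point to a correction of wording. A reader might infer from the mismatch that the trial is underpowered; the calculation shows the opposite.

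Second, the size of the discrepancy depends on a sidedness that the protocol does not state. The directional alternative and the reproduction of 51 and 64 favour one-sided; the ordinary p-values and 95% intervals in {20a} could suggest two-sided testing. This also stands. It would be tempting to report only the roughly 90% power and the 29-point detectable difference, but under a two-sided reading the figures are 84% and about 32 points, close to the planned 33. Both must be shown.

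Third, these powers are for an unadjusted comparison of two proportions, whereas the planned model adjusts for covariates and the primary population includes children with missing visits. That stands too. The protocol gives no covariate effects, so no power for the adjusted model can be quoted.

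Fourth, a reader might infer that the trial will claim a benefit beyond 5 points without having shown it. The documents do not support that: the objectives, hypotheses and analysis all describe ordinary superiority, and the margin may be no more than a software input. Nor can it be said that a null result would necessarily be misread, since the Discussion already warns that power may be insufficient because no study of similar equipment was available.

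None of this removes the contradiction. The margin is a stated input that determines the stated number, and the hypotheses in the same section exclude it.

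**Conclusion.** The inconsistency is real and should be corrected. The 80% belongs to a test of whether the reduction exceeds 5 points, which the plan does not run. For a test of no difference at 51 evaluable per arm and the assumed 54% versus 21%, power is about 90% (one-sided) or 84% (two-sided), so the stated figure errs on the cautious side by roughly 4 to 10 points.

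This rests on the protocol's own event rates, 20% dropout, the pooled normal-approximation test and no covariate adjustment. The one-sided reading is inferred, but the contradiction holds under either. The two nulls would lead to opposite conclusions only for a narrow band of results, and that matters only if the sponsor actually intends the margin.

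**What to change.** 1. Delete the superiority margin from the inputs under Sample size calculation.
2. State whether alpha = 0.0125 per comparison is one- or two-sided.
3. Restate the power, for example: 51 evaluable (64 randomised) per arm give about 90% power (one-sided 0.0125; 84% if two-sided) for 54% versus 21% in an unadjusted two-proportion comparison, and 80% power for 54% versus about 25% (about 22% if two-sided); power of the adjusted logistic model depends on covariate effects not available at planning.

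Only if the sponsor intends to claim a reduction of more than 5 points: write the margin into the null and alternative, and require the lower limit of the 97.5% interval for the risk difference (control minus intervention, standardised from the logistic model, one-sided 0.0125) to exceed 5 points. The size would then also depend on the test: the unpooled formula needs 51 per arm, a score-type test 55 (69 after dropout).

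The choice should be fixed and dated before the primary outcome is analysed, since choosing between the two nulls afterwards would depend on the data. The cost is a few lines of text, plus one standardisation step if the margin is kept. Enrolment does not change.

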#### Adjustment for dropout and attrition

Considering an anticipated dropout rate of 20%, the final required sample size per group is the following:Adjusted sample size per group: 64 participants.Total sample size for three groups: 192 participants.

#### Method for adjusting calculations for planned interim analyses

At this stage, no adjustments have been made for planned interim analyses. If interim analyses are planned in the study design, the sample size calculation should be adjusted using methods such as the O’Brien–Fleming or Pocock spending functions to control the overall type I error rate.

### Recruitment {15}

To ensure a sufficient sample size, we will implement a two-faceted recruitment strategy targeting schools and paediatric ophthalmology clinics.

School-based recruitmentWenzhou has a well-established vision screening system, with screenings conducted twice a year (March and September) in all schools. Researchers will collaborate with school health personnel and screening coordinators to identify children in the pre-myopic stage and invite them for further ophthalmic examinations at the hospital.Clinic-based recruitmentPediatric ophthalmologists will conduct preliminary screenings in outpatient clinics to identify children who meet the initial eligibility criteria. Parents of eligible children will receive detailed study information, and those expressing interest will be scheduled for a comprehensive baseline assessment to confirm eligibility.

During the recruitment phase, all potential participants and their guardians will receive comprehensive study information, including the research timeline, potential risks, and expected benefits, ensuring fully informed and voluntary participation.

